## Abstract

**Background:**

Postpartum depression remains a significant concern, posing substantial challenges to maternal well-being, infant health, and the mother-infant bond, particularly in the face of barriers to traditional support and interventions. Previous studies have shown that mobile health (mHealth) interventions offer an accessible means to facilitate early detection and management of mental health issues while at the same time promoting preventive care.

**Objective:**

This study aims to evaluate the effectiveness of the Leveraging on Virtual Engagement for Maternal Understanding & Mood-enhancement (LoVE4MUM) mobile app, which was developed based on the principles of cognitive behavioral therapy and psychoeducation and serves as an intervention to prevent postpartum depression.

**Methods:**

This single-blinded, pilot randomized controlled trial includes 64 mothers recruited from the postnatal ward and randomized using a 1:1 ratio to receive either postpartum care (treatment as usual) or postpartum care (treatment as usual) plus the self-guided LoVE4MUM mobile app. The primary outcome is the effectiveness of the mobile app at improving postpartum depression. Secondary outcomes are changes in the mental health literacy score and negative automatic thoughts, which are collected using a self-reported questionnaire.

**Results:**

Patient recruitment began on September 1, 2024. As of January 1, 2025, recruitment was successfully completed, with a total of 72 participants enrolled: 36 in the intervention group and 36 in the control group . The final results are anticipated to be available by March 2025, and publication is expected by the end of 2025.

**Conclusions:**

By examining the LoVE4MUM app alongside standard postpartum care, this pilot randomized controlled trial seeks to offer preliminary evidence on the potential of mHealth tools to improve maternal mental health as well as to reduce postpartum depression symptoms. The findings are expected to contribute to the future development of effective, accessible, and scalable interventions for mothers.

**Trial Registration:**

ClinicalTrials.gov NCT06366035; https://clinicaltrials.gov/study/NCT06366035

**International Registered Report Identifier (IRRID):**

PRR1-10.2196/63564

## Introduction

The global pooled prevalence of postpartum depression (PPD) was as high as 34% in a recent systematic review [1]. In Malaysia, the National Morbidity and Health Survey 2022 reported that 11.2% of mothers had depression [2] and an alarming 90% were unaware of their symptoms. Moreover, PPD results in detrimental consequences not only for the mother but also for the baby and their future bonding and relationship [3,4].

Meeting the increasing demand for mental health care is particularly challenging. These challenges encompass issues such as a lack of privacy, limited access to mental health experts, insufficient knowledge, and cultural stigma [5-8]. Consequently, mothers do not receive the necessary assistance that they require [5]. Mobile health (mHealth), a component of eHealth [9], has emerged as a crucial means to provide accessible health care solutions, especially with the advent of technologies like smartphones, web-based platforms, and text messaging [10,11]. These tools have become helpful for offering health care services and making health care more flexible, private, and readily available. This is particularly relevant in countries with high mobile internet penetration rates, such as Malaysia where rates of mobile internet coverage reached 128% in 2021 [12].

Interventions for depression range from pharmacotherapy to psychotherapy as well as lifestyle modifications [13]. Over the years, service delivery has evolved with the use of smartphone apps, web-based applications, and text messaging services to deliver therapeutic content [14,15]. Psychotherapies such as cognitive behavioral therapy (CBT) [16-18], mindfulness [19], and psychoeducation [20,21] using these technologies have previously been reported. A systematic review found that mHealth interventions can significantly improve depressive symptoms, highlighting their potential as accessible and cost-effective treatment options [22]. Additionally, more recent reviews concurred that mHealth interventions can effectively reduce PPD, as evidenced by improvements in Edinburgh Postnatal Depression Scale (EPDS) scores among these mothers [23,24]​​.

Women in the perinatal period are less likely to seek help for mental health issues than women at other life stages due to lower postpartum mental health literacy [25]. Mental health literacy has evolved from being defined merely as knowledge and beliefs about mental disorders to attitudes toward these disorders and efficacy in seeking help [26,27]. Kutcher et al [27] highlighted that poor mental health literacy leads to underutilization of mental health services, noting the critical role of help-seeking attitudes. mHealth platforms can boost mental health literacy by offering resources that heighten awareness of mental health issues, treatments, and self-care. For example, Chan et al [28] showed that mHealth is effective at enhancing mental health knowledge, attitudes, and behaviors, thus bridging the educational gap and reducing stigma. A systematic review emphasized the need for interventions to improve mental health literacy among perinatal women, due to a widespread lack of awareness about PPD symptoms, hesitance toward seeking professional help, a preference for informal support, and numerous other obstacles to accessing care, which are further compounded by marked stigma surrounding mental health issues [29].

Within the CBT framework, our thought processes are usually framed by our beliefs, which have a profound impact on how we feel and act in response to life's challenges [30]. Past experiences shape beliefs that can distort interpretations of events, leading to emotional disorders. In stress-triggering situations like the postpartum period, these beliefs trigger automatic negative thoughts and worsen depressive symptoms, underscoring the need to target these thoughts through depression management. By altering negative thought processes and maladaptive behaviors into more positive emotional outcomes, CBT offers improvements for depression management [31,32]. In addition, digital interventions, including exercises, thought diaries, and educational materials, facilitate the identification, confrontation, and modification of these negative cognitive patterns. A study demonstrated that smartphone-based CBT interventions could significantly reduce negative automatic thoughts and improve cognitive restructuring skills for users [33]. Mental health experts also advocate for short-term preventive CBT interventions, tailored for perinatal concerns, as a robust therapeutic strategy [34-36].

CBT’s traditional reliance on mental health professionals is challenged by cost and availability barriers. Due to health care personnel limitations, Mohammad-Alizadeh-Charandabi et al [37] highlighted the shortcomings of midwife-led phone interventions due to inconsistent quality and time constraints. In contrast, Niksalehi et al [38] effectively deployed structured automatic text messages with optional phone support, significantly enhancing depression scores and showcasing the potential of accessible, self-guided support. Complementing this, Carona et al [39] introduced a low-intensity, self-guided CBT program as an effective firstline intervention to help perinatal women, resulting in more improved depression scores in the intervention group than in the control group. Another study that used internet-based CBT [40] reported significant differences between the intervention and control groups.

It is noteworthy that the majority of studies on mHealth interventions were conducted in urban and academic settings in high-income countries [14]. Therefore, the generalizability of the outcomes is limited to the local population and might not apply to other settings such as Malaysia, which has a diverse cultural and religious background. Furthermore, these technologies frequently lack a user-centered design [41] and are primarily developed in western countries, which impacts their adaptability and sustainability in local contexts [14]. To culturally tailor appropriate mHealth interventions, meticulous development is required, engaging not only health care professionals to shape evidence-informed intervention priorities but also patients to enhance the effectiveness and widespread adoption of these interventions [42].

Initiatives in Malaysia include the TIARA MURNI project [43], which involves health care workers for its delivery. However, there is a notable absence of self-guided mental care solutions for mothers during the postpartum period especially in the Asian setting. This highlights an opportunity to improve mental health care access especially in areas with limited resources [38,44,45]. This study protocol intends to assess a user-centered, self-guided mental health app and compare it with standard postpartum care. It aims to determine the app’s preliminary effectiveness at improving depression and mental health literacy and addressing negative thoughts among mothers in the postpartum period.

## Methods

### Type and Design

This study is a single-blind, pilot randomized controlled trial with participants randomized using a 1:1 ratio.

### Study Location

The study includes postpartum mothers located in the postnatal ward of tertiary hospitals in the Selangor state of Malaysia. According to the Department of Statistics Malaysia, Selangor has the highest birth rate in the country, with a total of 95,211 live births in 2019 [46]. The National Morbidity and Health Survey 2022 survey indicated that urban mothers have a higher risk of depression. Considering Selangor’s birth statistics and status as a highly urbanized state, we considered it to be the ideal location for our research. We selected 2 hospitals from urban locations using a computerized random number generator.

### Ethics Approval and Ethical Considerations

Approval to conduct the study was obtained from the Medical Research and Ethics Committee, Ministry of Health Malays (ref number 24-00924-HPO, dated April 04, 2024). Written informed consent was obtained from all participants prior to their involvement in the study. Participants are fully informed of their right to opt out at any time without any consequences. All participant data are anonymized to ensure privacy and confidentiality. No identifiable information is collected nor stored during the study. Protective measures, including secure data storage, were implemented to safeguard participant information. Participants are compensated MYR 10 (US $2.15) for each questionnaire returned, to acknowledge their time and effort. Participation is entirely voluntary, without any form of coercion.

### Recruitment

Mothers were recruited from the obstetric wards by the investigators. Mothers received comprehensive information about the study, including its aims, procedures, risks, and benefits. Sufficient time was given to ensure informed consent was obtained in the ward. Those agreeing to participate were enrolled in the pilot randomized controlled trial, and reasons for refusal were documented.

Patients were screened for eligibility based on the study criteria. Mothers (1) scoring between 9 and 11 on the EPDS, (2) who had access to a smartphone, (3) who possessed home wireless internet or could access internet connectivity, (4) who planned to continue routine postpartum care in the government primary health facility, and (5) who were literate in both English and Malay were included in the study. Mothers (1) with a history of drug abuse; (2) who had been diagnosed with depressive illness in the current pregnancy; (3) who were undergoing treatment for depression, bipolar disorder, or any other psychiatric disease at the time of participation; and (5) whose infant experienced intrauterine death or death immediately after birth were excluded from the study.

### Randomization and Blinding

Participants were randomized (1:1) into 2 groups (ie, intervention and control groups). The researchers were blinded to the randomization process. Randomization was conducted by an independent assistant using a prearranged sealed opaque envelope. The envelopes contained a QR code linking to either a mobile app (the intervention group) or a WhatsApp communication channel (the control group). Both groups continue to receive treatment as usual (TAU) postpartum care.

### Intervention Group

The intervention group receives TAU postpartum care and the Leveraging on Virtual Engagement for Maternal Understanding & Mood-enhancement (LoVE4MUM) mobile app intervention.

The LoVE4MUM app represents an innovative self-guided approach to postpartum mental health care and offers a comprehensive, tailored intervention for maternal mental health during the postpartum period. It is available in English and the local Malay language. It was developed using a prior rigorous research process that included in-depth interviews with mothers who had symptoms of PPD and guidance from a multidisciplinary expert panel including clinical psychologists, psychiatrists, obstetricians, family health specialists, public health specialists, and epidemiologists with further input from previous literature [13,47-50]. This app-based intervention is grounded in psychoeducation, intrapersonal therapy, and CBT principles.

The app was validated by a panel of 4 experts. The content underwent detailed item-by-item validation to ensure its relevancy and clarity. In this face validation process, the majority of the items garnered unanimous approval, which was reflected in a content validity index and kappa coefficient of 1.00. Nevertheless, items 12 and 16 had content validity index and kappa scores <0.7, necessitating their revision to enhance relevancy within the module content. Additionally, item 18 was modified to provide better clarity. The expert panel reviewed the revisions and subsequently approved the finalized module. See Multimedia Appendix 1 for details of the validation process.

A linguistic expert translated the content into the Malay language to ensure that it was culturally and contextually appropriate. The app was developed on a self-developed website platform using a mobile phone interface. Snippets of the mobile app are available in Multimedia Appendix 2 and Multimedia Appendix 3.

The app is structured around 5 main modules that provide flexible and accessible support over a 6-week period. It does not require sequential module completion and allows for personalized pacing. Each module targets critical aspects of postpartum mental well-being and is delivered in several formats including video, infographics, notes, and worksheets. Each module takes approximately 20 minutes to 30 minutes to complete. Automated reminders incorporated into the app and linked to users’ emails encourage regular user engagement with app. The modules are described in Table 1.

**Table 1 table1:** 

Module	Module description	Skills learned	Worksheet
Module 1: Learn to Love Yourself	This module emphasizes self-care, establishing goals, and navigating social comparisons while addressing typical challenges like managing expectations, hospital admissions, and handling baby feeding and care. It aims to empower mothers to prioritize their well-being.	Self-care practices, goal formulation, effective communication for seeking help, and strategies for tackling common issues	Setting goals and listing things you love
Module 2: Understanding Postpartum Depression	This module offers foundational knowledge about postpartum depression, aiming to increase awareness and reduce stigma.	Identifying postpartum depression, seeking help, treatment options, and assertive communication with partners and family	—^a^
Module 3: Addressing Unhelpful Thinking	This module integrates cognitive behavioral therapy (CBT) concepts, guiding mothers to recognize and question negative thinking and understand how thoughts influence behaviors.	Identifying unhelpful thinking habits and mechanisms to improve thought patterns	Encourages describing specific situations and working on improving the associated thoughts
Module 4: Mood Tracker	This module engages mothers in monitoring their mood and provides strategies for mood improvement.	Identifying emotions, identifying healthier responses, and learning how to perform deep breathing	—
Module 5: I Need Help Now	This module guides users in accessing immediate calming techniques, help, and essential information for assertive communication with health care providers.	Calm breathing, communication with health providers, and information on seeking help	—

^a^Not applicable.

All data in the mobile app are stored in a password-protected, secured data cloud handled by the app developer. To register to use the app, participants must create a password that is requested after every time they sign in. Only administrative personnel have access to the encrypted password data.

### Control Group

Both groups receive TAU postpartum care during the study. According to The Malaysian Perinatal Care Manual (fourth edition), at least 5 postnatal home visits and 1 clinic visit are conducted for normal cases, and the frequency increases for high-risk mothers and babies [51,52]. Routine postnatal care services include lactation consultation in the ward and postnatal visits by health care workers at home. Each postnatal check should assess the mother's overall, psychological, and emotional health, asking about any concerns, and evaluate the baby's well-being, feeding, and development to promptly identify any issues [53]. Participants are advised that they are free to withdraw from the study at any point for any reason.

### Measurements

The study uses a questionnaire delivered online (Google form) and divided into 3 outcome measurement tools.

### Primary Outcome Measurement

The EPDS is a 10-item questionnaire extensively used to assess postnatal depression in both international and local contexts. It uses a 4-point Likert scale for responses, with higher scores indicating greater depressive symptoms. The scale has been translated into the Malay language [54], where a score of 11.5 was the optimum cut-off for 72.7% sensitivity, 95% specificity, and a positive predictive value of 80%. In our study, participants with an EPDS score ≥12 are categorized as having postpartum depressive symptoms.

### Secondary Outcome Measurements

#### Postpartum Depression Literacy Scale (PoDLiS)

The Postpartum Depression Literacy Scale (PoDLiS) is a 31-item, self-administered questionnaire developed by Mirsalimi et al [55] to assess the understanding of PPD. It evaluates 7 attributes of PPD literacy, including recognition, knowledge of risk factors and causes, self-care activities, available professional help, attitudes toward recognition and help-seeking, and information sources. Responses are scored on a 5-point scale, with attribute scores calculated by averaging related item scores. The Malay version of PoDLiS has acceptable reliability, with a Cronbach α of 0.73.

#### Automatic Thought Questionnaire (ATQ)

The Automatic Thought Questionnaire (ATQ), which is available in the Malay language [56], assesses the frequency of negative automatic thoughts linked to depression and anxiety. This 17-item scale asks respondents to rate the occurrence of specific negative thoughts over the past week on a scale from 1 to 5. Higher total scores indicate more frequent negative thinking. The scale’s internal consistency ranges from 0.83 to 0.93 [56]. The total score ranges from 17 to 85, with a higher score reflecting a higher frequency of negative thinking.

Data are conducted at baseline, 1 week postpartum, and 6 weeks postpartum using the Google form, which is delivered via either the mobile app or a Whatsapp number. The self-reported survey takes approximately 15 minutes to 20 minutes to complete. All answers are automatically storied in the Google drive, and only the research team has access to the data. The schedule of enrollment, interventions, and assessments is summarized in Multimedia Appendix 4 and Multimedia Appendix 5.

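### A 1-week ATQ form completed at about day 7 after birth partly recalls days before the app; estimate the ATQ effect from the 6-week value adjusted for baseline

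*Protocol article*

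**What the plan says.** All on the protocol article.

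- **Visit clock.** The Automatic Thought Questionnaire (ATQ) section states: "Data are conducted at baseline, 1 week postpartum, and 6 weeks postpartum using the Google form". Both follow-ups are counted from birth.
- **Recall period.** The same section says that the scale "asks respondents to rate the occurrence of specific negative thoughts over the past week on a scale from 1 to 5".
- **Recruitment point.** The Recruitment section states: "Mothers were recruited from the obstetric wards by the investigators", and on consent: "Sufficient time was given to ensure informed consent was obtained in the ward". The Abstract and the Study Location section specify the postnatal ward. One exclusion concerns fetal death or death of the infant straight after delivery, so eligibility is settled after the birth.
- **Start of access.** Under Randomization and Blinding: "The envelopes contained a QR code linking to either a mobile app (the intervention group) or a WhatsApp communication channel (the control group". No other route to the app is described.
- **Role of the ATQ.** The Abstract states: "Secondary outcomes are changes in the mental health literacy score and negative automatic thoughts". The ATQ is therefore a secondary outcome.
- **Analysis.** The Statistical Analysis section names a repeated measures ANOVA for time and treatment effects and places the comparison at 6 weeks. It does not say whether the 1-week wave is one of the time levels.

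**The concern.** Follow-up runs on one clock (birth) and the intervention on another (allocation). With a 7-day recall scale and a first follow-up 7 days after birth, the gap between the clocks falls inside the first recall window. A mother in the app arm is then asked to rate a week of which she spent part without the app.

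Two things are at stake. First, the 1-week ATQ contrast understates any early effect. Second, if that wave is a time level in the ANOVA, the weakened occasion enters the overall group effect, and an effect that is constant from first access can look as if it grows between 1 and 6 weeks. Negative automatic thoughts are what the app's cognitive behavioural content is meant to change, so a later, larger trial might well rely on that pattern.

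**Working it through.** The article gives no figure for the overlap, so there is none to reproduce.

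**Inputs.** From the article: recall window of 7 days; first follow-up at 1 week and second at 6 weeks after birth; app received at allocation, after birth. Not in the article: *d*, the day after birth on which the app is received, and *F*, the day on which the form is completed. Both are assumed below.

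**Share of the recall window that precedes the app.** The window runs from day *F* − 7 to day *F*, so

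share = max(0, *d* − (*F* − 7)) / 7.

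For a form completed on day 7 this is *d*/7:

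| *d* | Days of access (7 − *d*) | Share before app (*d*/7) | Effect retained (1 − *d*/7) |
|---|---|---|---|
| 1 | 6 | 1/7 = 14% | 0.86 |
| 2 | 5 | 2/7 = 29% | 0.71 |
| 3 | 4 | 3/7 = 43% | 0.57 |

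The last column also assumes that recall weights each day equally and that the effect is full and constant from first access.

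**Late forms.** With *F* = 8 and *d* = 1, the share is max(0, 1 − 1)/7 = 0. With *F* = 9 and *d* = 2, it is max(0, 2 − 2)/7 = 0. With *F* = 9 and *d* = 3, it is (3 − 2)/7 = 14%. A delay of a day or two can remove the overlap.

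**Six weeks.** With *F* = 42 the window covers days 35 to 42. The share is max(0, *d* − 35)/7 = 0 for any mother who receives the app during a postnatal ward stay.

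**If the 1-week wave is a time level.** Let the true effect be Δ, constant from first access, with *F* = 7 at the first follow-up.

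- Averaged over the two follow-ups, the group effect is Δ(2 − *d*/7)/2 = 0.93Δ, 0.86Δ or 0.79Δ for *d* = 1, 2 or 3, against Δ without overlap.
- If baseline is also a level, the average over three is Δ(0 + (1 − *d*/7) + 1)/3 = 0.62Δ, 0.57Δ or 0.52Δ, against 2Δ/3 = 0.67Δ without overlap. The proportional loss due to the overlap is the same.
- The apparent growth in effect from week 1 to week 6 is Δ·*d*/7 = 0.14Δ, 0.29Δ or 0.43Δ, although the true effect does not change.

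**The case against.** The strongest reply is that the stated comparison is at 6 weeks, where the overlap is zero, and that no 1-week contrast or early-effect claim is announced. That stands for the 6-week value. It does not settle the matter, because a repeated measures ANOVA needs more than one occasion and the text does not leave the 1-week wave out.

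A second reply is that time is a categorical factor, so a group-by-time term lets the effect differ between occasions, and the article never defines the treatment effect as an average over follow-ups. That is fair. The averages above therefore describe what happens only if a group main effect is reported. The group-by-time term avoids the averaging, but it carries the artificial growth instead.

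Third, the overlap depends on allocation and completion days that the article does not give, and the visit schedule is in an appendix that is not shown. That stands. A reader might infer that every 1-week form includes time before the app; a late form by a mother allocated early does not. Larger shares follow from later allocation, but nothing in the article supports a particular day.

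Fourth, the effect of a self-paced app may build slowly and be small in week 1 on any clock. That also stands: the absolute loss may be small, and the retained fractions hold only under a constant effect.

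**Conclusion.** The point holds as a narrow one. A past-week ATQ completed at about day 7 after birth partly covers time before the app. Under the assumed allocation days of 1, 2 or 3, that share is 14%, 29% or 43%; it falls to zero for sufficiently late forms. The consequence is attenuation of one interim value of a secondary outcome, plus dilution or a false time trend if that value enters the ANOVA as a time level.

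Three stronger readings are not supported:

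- **Bias towards one arm.** Both arms follow the same schedule, and randomisation makes the allocation day comparable between them.
- **A compromised 6-week result.** The 6-week recall window lies wholly after allocation. Nor can incomplete exposure at 6 weeks be argued from the statement "The app is structured around 5 main modules that provide flexible and accessible support over a 6-week period", since it does not say whether that period runs from allocation or from birth.
- **A wrong visit clock.** Timing by weeks since birth keeps postpartum age equal across mothers, which is a defensible choice in a postpartum condition. Recruitment was complete by January 1, 2025, so retiming visits is not a practical remedy for this trial.

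**What to change.** In the Statistical Analysis section, state that the ATQ treatment effect is the between-group difference at 6 weeks, adjusted for baseline ATQ (ANCOVA), with its 95% CI. State also that the 1-week ATQ is reported descriptively by arm, with days from allocation to form completion where those dates are available, and is not read as evidence for or against an early effect.

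This needs a change of wording and no new data: baseline and 6-week ATQ are already scheduled, and adjustment for baseline should add precision. It presumes that the baseline form is completed before the app is used. The article does not say that allocation and completion dates are recorded, so the days-since-allocation summary depends on what exists. The small downside is that the 1-week wave no longer contributes to the ATQ treatment estimate.

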Nevertheless, certain challenges remain. First, the reliance on self-reported measures may introduce bias, as participants may underreport symptoms due to stigma or discomfort. Second, as demonstrated with other mHealth interventions like the Happy Mother app, user engagement can be inconsistent, and low adherence rates may diminish the overall effectiveness of the intervention​ [77]. To address this, the LoVE4MUM app incorporates strategies to enhance user engagement, such as push notifications, scripts, and personalized feedback. Another critical aspect to consider is the influence of cultural factors on app engagement and perception, which may affect how Malaysian mothers interact with the app. Ensuring that the app’s content is culturally sensitive and tackles common misconceptions about PPD will be essential in maximizing its impact. Moreover, as a pilot trial, the sample size may not allow for definitive conclusions, and the study’s findings should be interpreted as preliminary evidence of the app's potential.

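### Outcome forms go through the app in one arm and WhatsApp in the other, so 6-week missing data may follow app engagement in one arm only

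*Protocol article*

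**What the plan says.** The delivery route of the outcome form is given at the end of the Methods subsection on the Automatic Thought Questionnaire. Outcomes are measured at three time points (at entry, then 1 and 6 weeks after birth), and the stated route is "using the Google form, which is delivered via either the mobile app or a Whatsapp number". That sentence does not say which arm has which route. The subsection Randomization and Blinding supplies the link: "The envelopes contained a QR code linking to either a mobile app (the intervention group) or a WhatsApp communication channel (the control group". No other collection route is described for either arm.

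Five further statements bear on the point.

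- The text under Table 1 describes access to the app: "participants must create a password that is requested after every time they sign in".
- Intervention Group mentions "Automated reminders incorporated into the app", linked to users' email and meant to encourage app use.
- Ethics Approval and Ethical Considerations gives MYR 10 per returned questionnaire, in both arms.
- Sample Size allows for 30% nonresponse, as one figure for both arms.
- The Discussion (Overview) warns, from experience with another app, that "user engagement can be inconsistent, and low adherence rates may diminish the overall effectiveness of the intervention".

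Statistical Analysis promises an intention-to-treat analysis using repeated measures ANOVA.

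**The concern.** Randomization makes the two groups comparable at entry. It does not make the two sets of responders comparable if they are selected by different mechanisms. A mother in the intervention arm who stops signing in may also lose sight of the form. A control mother has no app to disengage from, so her nonresponse has other causes. If app engagement is related to mood at 6 weeks, the observed intervention arm is a selected group in a way that the observed control arm is not.

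The primary outcome (EPDS) and both secondary outcomes share this route, so all three are exposed. The planned analysis adds to the exposure. In its standard form, repeated measures ANOVA uses only participants with every wave complete, so one missed form can remove a mother entirely, whatever the stated intention-to-treat principle.

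**Working it through.** **The plan's own figure.** Sample Size starts from 25 per arm and allows for 30% nonresponse: 25 / (1 − 0.30) = 35.7, rounded up to 36 per arm and 72 in total. This reproduces. It confirms that missing forms are expected, at one common rate. Changing the delivery route does not alter it.

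**Inputs for the illustration.** From the documents: 36 per arm, 30% nonresponse (70% response), planning effect 0.43. Assumed, because the documents are silent: the response rate r in the app arm (0.5 to 0.9), the correlation ρ between responding and having a better 6-week score (0 to 0.5), and control nonresponse unrelated to outcome.

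**Formula.** With no true effect and a standardized outcome, a normal selection model gives a spurious difference (app minus control; negative favours the app) of

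bias = −ρ × φ(z) / r, where z is the (1 − r) quantile of the standard normal and φ its density.

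For r = 0.70: z = −0.524, φ(z) = 0.348, φ(z) / r = 0.497. So ρ = 0.3 gives −0.15 and ρ = 0.5 gives −0.25.

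| App-arm response | ρ = 0 | ρ = 0.1 | ρ = 0.3 | ρ = 0.5 |
|---|---|---|---|---|
| 90% | 0 | −0.02 | −0.06 | −0.10 |
| 70% | 0 | −0.05 | −0.15 | −0.25 |
| 50% | 0 | −0.08 | −0.24 | −0.40 |

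A negative ρ, where mothers who feel worse keep opening the app, gives the same sizes with the opposite sign.

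**Effect on the test.** In a simulation with no true effect (36 randomized per arm, 8,000 runs, t test at 6 weeks at the two-sided 5% level, 90% random response in controls), the false-positive rates were:

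| App-arm response | ρ | False-positive rate |
|---|---|---|
| 70% | 0 | 4.6% |
| 70% | 0.3 | 8.5% |
| 70% | 0.5 | 15.3% |
| 50% | 0.3 | 12.4% |
| 50% | 0.5 | 25.9% |

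With 70% response and ρ = 0.3 in both arms, the selection cancelled and the rate was 5.0%. So the trouble is a difference in selection between the arms, not nonresponse as such.

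**The case against.** The strongest reply is that a different route is only a possible source of bias. Bias also needs response to depend on app engagement, and engagement to be related to the 6-week score. The article establishes neither. That stands, and it is why the point is put as a risk.

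Several supporting objections also have weight.

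- Nothing says that a mother who stops using the modules cannot see the form, and opening the app to reach a form is not the same as using the modules.
- Control mothers must also scan a QR code and keep reading a channel, so their route is not free of effort.
- Payment per questionnaire applies to both arms.
- The app's email-linked reminders could bring some mothers back. However, they are described as prompting app use, not as carrying the form link, and they exist in one arm only. They soften the difference between arms without removing it.
- The plan allows the same 30% nonresponse in both arms, and equal selection would cancel. But an equal rate does not imply an equal mechanism.

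A reader might infer more: that the comparison is biased, that the bias favours the app, or that it takes away a set share of the planned effect. One such sum is 0.30 nonresponse × a 2-point EPDS gap = 0.6 points, or 35% of 1.72 points (0.43 × an SD of 4). The gap and the SD are both assumptions, and the sum treats every nonresponder as a non-user and control loss as harmless. The documents support none of these statements. The app includes a mood tracker and an immediate-help module, so mothers who feel worse could well be the ones who stay.

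A reader might also infer that the separate channels defeat the blinding in "This study is a single-blind, pilot randomized controlled trial". That is a separate and weaker point. The article does not claim that mothers were blinded, the answers are self-reported and stored automatically, and the Discussion already lists self-report as a limitation.

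**Conclusion.** The point holds as a risk of bias. The arm-specific route follows from two sections read together, and in the intervention arm that route is the intervention itself. Missing 1-week and 6-week data may therefore depend on app engagement in one arm only, for the EPDS, the PoDLiS and the ATQ.

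The size and direction cannot be derived from the documents. At 70% app-arm response the illustration runs from 0 to 0.25 SD, against a planning effect of 0.43, and the sign can go either way. It rests on an assumed correlation between response and outcome, on ignorable control nonresponse, and on a simple comparison at 6 weeks in place of the planned ANOVA. The article itself calls the results preliminary. That limits the claims that can be made from the trial, but it does not make an observed difference easier to interpret.

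**What to change.** For every form still outstanding, send the same Google-form link to both arms by one route outside the app, with the same timing and the same reminders. This needs one common message and no change to the sample size, which stays at 72. The small cost is that the form is no longer prompted inside the app. A common route does not guarantee equal selection, but it removes the dependence that the design itself creates.

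The Results section says that recruitment was complete by January 1, 2025, with results expected by March 2025, so many forms may already be in. For those:

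- Report the number of forms returned by arm and wave and, in the app arm, by whether the mother logged in.
- Run a missing-not-at-random sensitivity analysis, for example giving app-arm nonresponders values like those of the controls. If 30% of the app arm is missing and is set to the control mean, the responder difference is multiplied by 0.70. Because the direction is unknown, shifts both ways should be shown.
- State in the report that the collection route differed by arm.

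These steps use data that the app and the form should already hold, and cost only analysis time.
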